## **1. General information**

### **Title of the study**

Identification of predictive parameters of difficult intubation in patients to be submitted to thyroidectomy

Protocol Version 1.4 - 09 February 2017

## **2. Background**

### **2.1 Definitions**

For difficult intubation [1], we mean a procedure that has been characterized by a difficult laryngoscopy or has required at least four attempts or more than five minutes for its execution regardless of the degree of experience of the anesthesiologist.

Difficult laryngoscopy refers to the impossibility of highlighting the glottis with the conventional curved blade laryngoscope. It corresponds to grades 3 and 4 of the classification of Cormack and Lehane (Annex 1) in which it is possible to highlight respectively only the epiglottis or the language alone.

### **2.2 Dimension of the problem**

The incidence data reported by the literature on difficult airway control are often contradictory because they have suffered in the past from the lack of univocal definitions. 30% of all accidents related to anesthesia are sustained by difficulty in controlling the airways, 70% of these accidents resulted in death or permanent brain damage. The incidence of difficult intubation in the general population is between 0.5% and 20%.

### **2.3 Difficulty**

prediction The prediction of difficulties is based on the objective examination of the patient with evaluation of the following parameters:

- measurement distance interdental
- test of Mallampati (Annex 2 )
- visibility of pharyngeal structures
- measure of chin-thyroid distance
- measures maxillary prognathism
- global neck motility

The prediction of difficulty or inability to intubate is based on the modest deviation of several parameters or on the serious alteration of a single parameter. In particular, the literature [1] considers that the following parameters are

- distance <2 cm
- severe maxillary prognathism
- mallampati 4

- fixed neck in extension
- scarring or severe actinic effects on the lingual floor

### **2.3 Forecast of difficulties and thyroid pathology**

Patients with thyroid disease represent a particular class of patients with regard to tracheal intubation due to the close anatomical contiguity between the thyroid and the trachea: it is therefore clear that an enlargement of the thyroid gland can cause dislocation and compression of the airways.

Studies have already been carried out on airways and thyroid pathology [2,3,4,5,6]. The percentage of difficult intubation was variable from 0% [4] to 12,9% [5]. The criteria analyzed in literature are: interdental distance, migraine test, thyromenton distance, presence of receding chin, neck mobility, weight, age, presence of tracheal deviation to RX, presence of tracheal stricture at RX, malignant character of thyroid pathology, diameter of neck, presence of mediastinal goiter, glandular volume.

None of the studies in the literature has analyzed all these characteristics, but each has focused on different characteristics, thus leaving the lack of a study that globally analyzes these characteristics in this class of patients.

Furthermore, the conclusions are conflicting; characteristics such as opening of the mouth, moulding, thyromenton distance, receding chin, neck mobility, tracheal deviation, malignant nature of thyroid pathology and tracheal stenosis have been significant in some studies and not significant in others; this finding can be justified by the low number of studies, in fact the highest number of studies is 326 patients [3] and the one with the lowest number of 50 patients [4].

### **2.5 Rationale of the study**

The main strategy to avoid accidents of airway control is the planning and prediction of possible difficulties [7,8].

Although there are several scores on the prediction of difficulty for difficult intubation, there is little that exists regarding the class of patients with goiter [2,3,4,5,6].

The rationale is therefore to assess whether the predictive criteria of difficult intubation already validated for the population are also valid for the population suffering from thyroid disease, in addition to assessing whether there are peculiar characteristics of this population (neck diameter, tracheal displacement, mediastinal goiter) that can help in predicting the difficulty of intubation.

The study therefore aims to overcome the critical issues of previous studies both in terms of sample size, and as regards the overall analysis of parameters concerning difficult intubation without dwelling, unlike previous studies, only on some of them.

### **3. Objectives of the study and hypothesis**

#### **3.1. Primary objective and hypothesis**

Evaluation incidence difficult intubation in the population with thyroid pathology compared to the data provided by the literature in the general population

#### **3.2. Secondary objective**

Identification of parameters or patterns of predictive parameters of difficult intubation during thyroidectomy.

The examination of NC/TMD for predicting DTI in patients undergoing thyroid surgery.

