## **5. Materials and methods**

During the routine anaesthesiology visit, upon collection of the consent, the following parameters will be recorded on the data sheet.

- Opening mouth (cm)
- Distance thyreomental (cm)
- Test of Mallampati (Annex 2)
- Mobility of the neck (<80 °; 80-90 °; > 90 °)
- Inability to prognath
- Body weight (kg)
- History of previous intubation difficult
- Tracheal deviation to the chest radiography
- Diameter of the goiter (cm)
- Presence of mediastinal goiter
- Benign or malignant nature of the thyroid pathology

On the day of the surgical intervention after tracheal gold intubation the presence or absence of difficulty in the maneuver will be reported on the data sheet ; in particular:

- Cormack Scale (Annex 1)
- Number of attempts necessary to successfully perform the intubation
- Time elapsed since the induction of general anesthesia and intubation successfully
- If advanced airway instrument were used and which ones

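### Section 3.2 makes NC/TMD a predictor to be examined, but no neck-size item is on the section 5 data list, so the ratio cannot be computed as written

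*Protocol*

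**What the plan says.** Protocol section 3.2 has two sentences. The first is a general aim: to find parameters, or patterns of parameters, that predict difficult intubation. The second is specific: "The examination of NC/TMD for predicting DTI in patients undergoing thyroid surgery". None of the abbreviations in it is expanded there or elsewhere in the protocol.

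Section 5 (Materials and methods) states that at the routine anaesthesiology visit "the following parameters will be recorded on the data sheet", and then gives 11 preoperative items. Three bear on this point:

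- "Distance thyreomental (cm"), the thyromental distance;
- "Mobility of the neck (<80 °; 80-90 °; > 90" degrees), a range-of-motion item in three bands;
- "Diameter of the goiter (cm"), a dimension of the gland.

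Neck size appears in the background. The section 2.3 on thyroid pathology includes it among the criteria studied in the literature: "diameter of neck, presence of mediastinal goiter, glandular volume". Section 2.5 then names it among the "peculiar characteristics of this population (neck diameter, tracheal displacement, mediastinal goiter") that the study means to assess.

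Section 4.1 adds that only information normally obtained at a routine anaesthetic visit will be recorded.

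**The concern.** A ratio needs both its terms for each patient. Section 3.2 commits the study to a ratio, and the section 5 list appears to supply only the denominator. If so, the objective and the data list contradict each other.

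This is not a detail that can be left to a statistical analysis plan. Such a plan can choose a cut-point, a model or an accuracy measure for NC/TMD, but it cannot create a variable that was not collected. Neck size before thyroidectomy also cannot be measured once the gland has been removed. Each patient who passes through the visit without the measurement is lost to this aim, unless the value happens to be in the clinical record, which the protocol does not say.

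**Working it through.** The protocol gives no figure for this point, so there is none to reproduce. The check sets the terms of the ratio against every listed variable.

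**Assumed reading.** NC is neck circumference and TMD is thyromental distance. DTI is taken to be difficult tracheal intubation.

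**Preoperative items in section 5, in order:**

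| Item | Supplies NC? | Supplies TMD? |
|---|---|---|
| Mouth opening | no | no |
| Thyromental distance, cm | no | yes |
| Mallampati test | no | no |
| Neck mobility, three angle bands | no (movement, not size) | no |
| Inability to prognath | no | no |
| Body weight | no | no |
| Previous difficult intubation | no | no |
| Tracheal deviation on chest film | no | no |
| Goiter diameter, cm | no (gland, not neck) | no |
| Mediastinal goiter | no | no |
| Benign or malignant nature | no | no |

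**Items on the day of surgery.** Cormack grade, number of attempts, time to intubation and advanced devices used. None is a neck size.

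**Rest of the protocol.** Neck diameter is mentioned in sections 2.3 and 2.5 only as a candidate predictor. No section provides for measuring neck circumference or neck diameter.

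**Result for the ratio.** One of its two terms is recorded. NC/TMD is therefore computable from the listed variables in 0% of patients. That share does not depend on the sample size, so the 515 of section 5.2.1 plays no part in the argument.

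**Result for the rationale.** Section 2.5 gives three characteristics as examples. Tracheal displacement is covered by tracheal deviation, mediastinal goiter is listed, and neck diameter is not. Two of three are recorded.

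**Sensitivity to the reading of NC.** If NC meant neck diameter or any other neck size, the numerator would still be absent, because no neck-size item is listed under any name.

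**The case against.** **NC is undefined, so its absence cannot be shown.** The reading is an assumption. The conclusion needs only that NC is some neck size, and none is listed. An unexpanded predictor in a stated objective needs correcting in any case.

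**Goiter diameter may be a mistranslation of neck diameter.** This is the best counter-argument. The English is visibly a translation, and in the section 5 list goiter diameter stands between tracheal deviation and mediastinal goiter, where section 2.5 would lead one to expect neck diameter. It cannot be excluded. But the current text says goiter, sections 2.3 and 2.5 treat neck diameter as its own item, and staff following the list would measure the gland. Even if the explanation is right, the list would hold a diameter and not a circumference, and the text would still need correcting.

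**The list may not be the whole data sheet.** The form is not reproduced in the protocol, so a neck measurement could be on it. This stands as a limit: the finding concerns the protocol as written.

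**Stronger readings that a reader might infer, and that the documents do not support:**

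- *That no neck measurement is taken at all.* Neck mobility is recorded. What is missing is neck size.
- *That the secondary objective fails as a whole.* The first sentence of section 3.2 can be pursued with the 11 listed items.
- *That the study breaks a promise by also leaving out other criteria named in section 2.3, such as receding chin, tracheal stricture or gland volume.* That passage summarises the literature. Its remark "None of the studies in the literature has analyzed all these characteristics" describes earlier studies and does not commit this one to record every item. Section 2.5 promises an overall analysis in looser terms. Age, also absent from the list, must be known for eligibility; jaw configuration and gland size are partly covered by inability to prognath and goiter diameter.

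**Conclusion.** The point holds in a narrow form. The NC/TMD aim in section 3.2 and the data list in section 5 contradict each other: the denominator is recorded, the numerator is neither defined nor recorded, and the ratio cannot be computed for any patient from the listed variables. The neck diameter named in section 2.5 is unrecorded too.

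In extent, one of the two sentences of the secondary objective is blocked. The primary objective, the incidence of difficult intubation, is untouched, and so is the general search for predictors, apart from the missing neck diameter.

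The conclusion rests on two assumptions: that NC is a neck size, and that the section 5 list describes the data sheet completely. Within its extent it matters, because the gap is in data collection and cannot be closed at the analysis stage.

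**What to change.** 1. Expand NC and TMD where they first appear in section 3.2.
2. Add neck circumference to the section 5 visit list and to the data sheet, in cm, with a fixed measurement level and head position.
3. Define NC/TMD as neck circumference (cm) divided by thyromental distance (cm).
4. Reconcile the addition with section 4.1. Either state that neck circumference is part of the routine anaesthetic visit at this hospital, or amend the sentence that limits recording to routine information. The protocol does not say which applies.
5. If goiter diameter was meant to be neck diameter, correct the item. If it was not, align section 2.5 with what is recorded.
6. If neck circumference will not be measured, delete the NC/TMD sentence from section 3.2.

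The cost is one line on the data sheet and one brief tape measurement per patient. Patients seen before the change would be excluded from the NC/TMD analysis, and their number should be reported. Deleting the aim costs no data but gives up the question.

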#### **4.1 Enrollment**

This prospective observational study will be conducted in the operating rooms of the first and second floors of the Company's hospital Hospital of Padua.

All patients requiring thyroidectomy will be enrolled.

No clinical decision will be made based on the data collected for this study. In fact, during the study only information that is normally detected during a routine anesthetic visit will be recorded.

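### The NC/TMD secondary objective lacks its numerator: NC is undefined, and the list of parameters to be recorded contains no neck circumference or neck diameter

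*Protocol*

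**What the plan says.** Section 3.2 (Secondary objective) has two parts. The first is a general search for parameters, or patterns of them, that predict difficult intubation. The second is specific: "The examination of NC/TMD for predicting DTI in patients undergoing thyroid surgery". The protocol expands neither NC nor TMD.

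Section 5 (Materials and methods) says that at the anaesthesiology visit "the following parameters will be recorded on the data sheet", and then gives 11 items. Three matter here: "Distance thyreomental (cm)", "Mobility of the neck" (in three bands of degrees) and "Diameter of the goiter (cm)". Four more items are recorded at intubation.

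Section 2.5 (Rationale) says the study will also assess "peculiar characteristics of this population (neck diameter, tracheal displacement, mediastinal goiter)". Section 4.1 (Enrollment) adds that "during the study only information that is normally detected during a routine anesthetic visit will be recorded".

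**The concern.** A ratio needs both of its terms for every patient who enters the analysis. The protocol gives NC/TMD an objective of its own, yet its list of recorded parameters supplies only the denominator. If staff follow that list, the ratio will be missing throughout and the objective cannot be reported. A statistical analysis plan could not repair this, because it decides how to analyse what was measured and cannot supply a variable that was not.

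Leaving NC undefined adds a second problem. Even where staff do measure the neck, the protocol gives no quantity, anatomical level or unit, so values may not be comparable between patients.

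**Working it through.** No arithmetic is involved and there is no stated figure to reproduce. The check compares what the objective needs with what the protocol says will be recorded.

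**What is needed.** NC/TMD = NC ÷ TMD. With NC read as neck circumference and TMD as thyromental distance, two lengths per patient are required.

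**What is listed in section 5.**

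- Eleven pre-operative items: mouth opening, thyromental distance, Mallampati test, neck mobility, inability to prognath, body weight, history of difficult intubation, tracheal deviation on chest radiography, goiter diameter, mediastinal goiter, and benign or malignant pathology.
- Four intubation items: Cormack grade, number of attempts, time to intubation, and any advanced airway instruments used.

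**Matching the two.**

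| Term or candidate | In the list? | Usable? |
|---|---|---|
| TMD | Yes, in cm | Yes, as denominator |
| Neck circumference | No | – |
| Neck diameter | No item under that name | – |
| Neck mobility | Yes, three bands of degrees | No: a range of motion, not a size |
| Goiter diameter | Yes, in cm | No: a dimension of the gland, not of the neck |

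With TMD known and NC absent, the ratio is undetermined. Replacing NC by goiter diameter would give a different predictor from the one named in section 3.2. The result does not hinge on the exact expansion of NC, since no listed item fits either a neck circumference or a neck diameter.

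**Other possible sources.** Section 5.1 (Data collection) describes a form and patient coding but adds no variable. Section 4.1 limits recording to routine-visit information and names no neck size.

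**Rationale against list.** Of the three characteristics in section 2.5, tracheal displacement and mediastinal goiter have evident counterparts in section 5. Neck diameter has none that is clear. The section on thyroid pathology (the second one numbered 2.3) also counts the diameter of the neck among the criteria studied in the literature, and says that no earlier study analysed all of those criteria.

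**The case against.** The best reply is that absence from the list does not prove absence from the data. Section 5 never says that only these items are recorded. The list is visibly incomplete, since it omits age, which is an eligibility criterion and one of the literature predictors. The form itself is not shown. This stands as a limit on the claim. A reader might infer that the ratio could never be computed for any patient; the documents support only that the protocol does not provide for it.

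Four other stronger readings also go too far:

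- *Section 4.1 rules the measurement out.* It does so only if neck circumference is not routine at this hospital, and the protocol does not say.
- *Neck diameter is certainly not recorded.* The text reads as a translation, and goiter diameter sits in section 5 between the counterparts of the other two characteristics in section 2.5. It may be the same item rendered differently. That is inference, and a goiter diameter is still not a neck circumference, but the wording leaves the matter open.
- *Nothing about the neck is measured.* Neck mobility is recorded. What is missing is a measure of neck size.
- *The loss could not be repaired afterwards.* The protocol says nothing about how surgery changes the neck or how complete the charts are. If the measurement is routine, chart values might cover most patients.

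It is also fair to say that the primary objective, the incidence of difficult intubation, and the general predictor objective can go ahead with the listed items.

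None of this removes the mismatch. The protocol governs what is collected, and it should list the variable that its own objective requires.

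**Conclusion.** The point holds as an internal inconsistency. One of the two secondary objectives in section 3.2 cannot be analysed from the data listed in section 5, because the numerator of NC/TMD is neither defined nor listed. On the listed items alone the ratio is available for no patient, whatever the sample size. The rationale's neck diameter likewise has no clearly matching item.

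The conclusion assumes that NC means neck circumference (any measure of neck size leads to the same result), that TMD means thyromental distance, and that data are collected as section 5 describes. It does not show that the measurement was in fact omitted in practice. It leaves the primary objective untouched. It should be settled before enrolment, or as early as possible, because every patient enrolled under the present list may lack the value.

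**What to change.** 1. In section 5, add: Neck circumference (cm), measured pre-operatively at one stated level.
2. In section 3.2, spell out the abbreviations and define NC/TMD as neck circumference divided by thyromental distance, both in cm.
3. In section 2.5, align neck diameter with the section 5 list, so that it is clear whether neck circumference, goiter diameter or a separate item is meant.
4. If the measurement is not part of the routine visit locally, amend the sentence in section 4.1 that limits recording to routine information.
5. If enrolment has begun, restrict the NC/TMD analysis to patients with a pre-operative measurement and report that number.
6. If neck circumference will not be measured, delete the objective.

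The cost is one short extra measurement per patient and a minor amendment. The sample size need not change on this account.

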### **4. Inclusion / exclusion**

#### **criteria Inclusion criteria**

- ✓ Surgical program of total or partial thyroidectomy
- ✓ Age > 18 years

#### **Exclusion criteria**

- ✓ Age < 18 years
- ✓ Expected difficult intubation

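### The exclusion of expected difficult intubation makes the enrolled group narrower than the population named in the objectives, so incidence is understated whenever the preoperative assessment is informative

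*Protocol*

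**What the plan says.** The primary objective (section 3.1) is "Evaluation incidence difficult intubation in the population with thyroid pathology compared to the data provided by the literature in the general population". The secondary objective (section 3.2) is "Identification of parameters or patterns of predictive parameters of difficult intubation during thyroidectomy". Section 2.5 gives as the rationale to "assess whether the predictive criteria of difficult intubation already validated for the population are also valid for the population suffering from thyroid disease". Neither these statements nor the title is limited to unanticipated difficulty.

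The exclusion criteria in section 4 nevertheless remove patients with "Expected difficult intubation", and no rule says who meets that description. Section 4.1 then says: "All patients requiring thyroidectomy will be enrolled".

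The first of the two sections numbered 2.3 describes how difficulty is foreseen. The prediction "is based on the modest deviation of several parameters or on the serious alteration of a single parameter", and Mallampati 4 is among the listed examples. Section 5 records much the same measurements as candidate predictors, together with "History of previous intubation difficult". Section 8 names only the single-centre design as the main limitation.

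**The concern.** The primary objective is a count of difficult intubations in thyroid patients, set against published general-population figures. The exclusion takes out the patients in whom the anaesthetist already foresees difficulty. What remains to be counted is unanticipated difficulty in a pre-screened group, yet it would be reported as the incidence in thyroid disease.

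A real excess in thyroid patients could be hidden. If there were no true excess, an apparent deficit could be produced.

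The secondary objective suffers as well. Asking whether validated criteria work in these patients is harder once many of those clearly positive on the criteria have been removed. No later analysis can recover patients who were never enrolled, so a statistical analysis plan could not repair this.

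**Working it through.** **1. Overlap between the exclusion and the predictors.**

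| Basis of expectation (first section 2.3) | Recorded as a predictor (section 5) |
|---|---|
| Interdental distance | Mouth opening |
| Mallampati test | Mallampati test |
| Chin-thyroid distance | Thyromental distance |
| Prognathism | Inability to prognath |
| Neck motility | Neck mobility |
| Visibility of pharyngeal structures | No separate item; the Mallampati classes in the annex describe it |

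Section 5 also records weight, previous difficult intubation, tracheal deviation, goitre diameter, mediastinal goitre and benign or malignant nature. These are not on the section 2.3 list.

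**2. The plan's own figure.** Section 5.2.1 gives 515 patients for a 4-point difference, alpha 5%, power 95% and 5% dropout. It states neither base rate nor the direction, so 515 can be neither confirmed nor refuted. A two-sided one-sample test gives 500 to 528 for about 4.6-4.95% versus 8.6-8.95%, after dividing by 0.95. The present point does not depend on this number.

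**3. Direction of the bias.** Let I be the true incidence in all thyroidectomy patients, f the share excluded, and PPV the share of those excluded who would have been difficult.

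- Observed incidence = (I − f·PPV)/(1 − f)
- Loss = I − observed = f·(PPV − I)/(1 − f)

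The loss is positive exactly when PPV > I, that is, when the assessment is better than chance.

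**4. Size, under assumptions.** The document gives neither f nor PPV. Assume I = 8% and three levels of sensitivity (Se) and specificity (Sp).

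- Excluded f = I·Se + (1 − I)(1 − Sp)
- Observed = I(1 − Se)/(1 − f)

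| Se / Sp | Excluded | Observed incidence | Loss (points) | Implied PPV |
|---|---|---|---|---|
| 30% / 95% | 0.024 + 0.046 = 7.0% | 0.056/0.930 = 6.0% | 2.0 | 34% |
| 50% / 90% | 0.040 + 0.092 = 13.2% | 0.040/0.868 = 4.6% | 3.4 | 30% |
| 70% / 85% | 0.056 + 0.138 = 19.4% | 0.024/0.806 = 3.0% | 5.0 | 29% |

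A wider grid takes I from 5% to 12.9% (the latter is the highest thyroid figure quoted in the protocol), f from 2% to 10% and PPV from 20% to 70%, keeping f·PPV < I. The loss then runs from about 0.1 to 6.9 points:

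- Low end: I = 12.9%, f = 2%, PPV = 20% gives 0.02 × 0.071/0.98 = 0.14 points.
- High end: I = 8%, f = 10%, PPV = 70% gives 0.10 × 0.62/0.90 = 6.9 points.

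**5. Effect on power.** Assume a fixed reference of 5%, a true thyroid incidence of 9%, a two-sided one-sample test and 515 × 0.95 ≈ 489 evaluable patients.

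| f / PPV | Observed incidence | Power |
|---|---|---|
| no exclusion | 9.0% | 94.5% |
| 2% / 30% | 8.6% | 90% |
| 5% / 30% | 7.9% | 79% |
| 5% / 50% | 6.8% | 47% |
| 10% / 30% | 6.7% | 41% |

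**6. Effect on the odds ratios.** Section 5.2.1 plans multiple logistic regression. A simulation with two predictors, each with a true odds ratio of 2.01, excluded the top 7%, 13% or 19% on their sum.

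- Adjusted odds ratios stayed at 2.00-2.02, while standard errors rose by 32-78%.
- The univariate odds ratio fell from 1.96 to 1.68-1.53.
- When the expectation also used risk information outside the model, the adjusted odds ratio fell from 1.93 to 1.71-1.56.

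**The case against.** The strongest defence is that the exclusion is deliberate. Section 2.1 defines difficult laryngoscopy by the conventional curved blade, and some patients with anticipated difficulty may never have that view recorded. This is a fair reason to study unanticipated difficulty, but the title, objectives and comparator would then have to say so, and they do not.

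Section 4.1 can also be read as all eligible patients; taken literally it would override the age limit too. The conflict with section 4.1 is therefore supporting evidence, and the mismatch with the objectives carries the point. Likewise, section 2.3 does not list previous difficult intubation as a basis for expectation, so treating those patients as excluded is an inference.

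A reader might infer several stronger things that the document does not support:

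- **That the cases to be counted are all removed.** Only anticipated ones are. In the three scenarios above, 30-70% of difficult cases remain.
- **That the adjusted odds ratios must shrink, or that a null result for Mallampati or mouth opening would be an artefact.** Selection on covariates in a correctly specified model mainly costs precision. Lost power is the safer statement.
- **That the predictors become nearly constant.** If only extremes such as Mallampati 4 are excluded, lower classes still vary, and the thyroid-specific features are not on the section 2.3 list.
- **That the bias equals the whole 4-point difference.** Only the most extreme of the three scenarios passes 4 points.
- **That the comparator is known to differ.** The protocol is silent on this, and the cited sources are not at hand.

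**Conclusion.** The concern holds in this form: an undefined exclusion makes the enrolled group narrower than the population in the title and objectives. The direction is firm. Incidence is understated relative to the stated target whenever the preoperative assessment is better than chance.

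Confidence in the size is low, because the criterion is undefined and every input to the size (true incidence, accuracy of the assessment, share excluded) is assumed. The plausible loss runs from negligible to more than the design difference. Comparability with the general-population figures is not shown.

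For the predictor analysis, expect wider intervals, weaker univariate associations and poorer discrimination (the protocol names no discrimination measure). Bias in the adjusted odds ratios is conditional on misspecification or on risk information outside the model.

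**What to change.** Reconcile sections 3.1, 3.2, the exclusion criteria and section 4.1 before enrolment.

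**Preferred.** Remove the exclusion and enrol consecutive thyroidectomy patients. Add one yes/no field for whether difficulty was anticipated at the visit, with a definition of that judgement. Report incidence overall and split by the field, and fit the predictor analysis on the full cohort. Count patients without a conventional-blade Cormack grade separately, and show incidence with all of them and then none of them classed as difficult. The width of that band equals the ungraded share of all patients.

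**Otherwise.** Keep the exclusion, define it, and log how many patients it removes. Restate the title, objectives and conclusions as unanticipated difficult intubation. Use a comparator with the same exclusion, or state that the comparison is not like with like.

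**Cost.** A protocol amendment and one tick-box, or a rewording and an exclusion log. The study is observational and sections 4.1 and 6 state that no clinical decision rests on its data, so neither route alters care. The downside of the preferred route is the handling of ungraded patients, which is small only if they are few.
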